**Table 1:** Overview of measurements, timing, and definitions.

**Table 2:** Overview of data entered in the online register by both physician and patients.

**Figure 1:** Participating ear, nose and throat departments in Jutland are: Aalborg University Hospital and Thisted Hospital. Gødstrup Hospital. Esbjerg Hospital. Lillebælt Hospital, Vejle. Sønderjyllands Hospital, Sønderborg.

**Figure 2:** Eligible patients who have signed a written consent are included in the study. Patient information is entered into the tonsil database by the surgeon. The computer randomly assigns patients to two study arms via block randomization. The control group undergoes standard cold steel tonsillectomy. The investigational group receives tonsillectomy with impedance dependent tissue sealer device. The per-operative procedure is equal for both groups as well as postoperative recommendations. The patients or their caregivers answer daily questionnaires on their mobile device regarding adherence to postoperative recommendations; pain scores on a Likert scale for adults/Wong-Baker scale for children; activity level; food consumption; unscheduled contacts to the health care system; return to school, work or childcare; satisfaction with the procedure; health related quality of life on the EQ5D-SL questionnaire; and quality of taste and smell. If post-tonsillectomy hemorrhage, infection, rehospitalization for rehydration occurs the doctor will input a detailed account in the database.

**Randomized controlled trial on Cold Steel versus Impedance Dependent Tissue Sealer tonsillectomy comparing postoperative morbidity**

Authors: [name]^1^; [name]^1^; [name]^3^; [name]^4^; [name]^5^; [name]^6^; [name]^1,2^.

Affiliations: 1 University Clinic for Balance, Flavour and Sleep, ENT department Gødstrup, [name], 2 Department of Clinical Medicine, Aarhus University, [name], 3 Ear, nose and throat department, Aalborg University Hospital, [name]; 4 Ear, nose and throat department, Sygehus Sønderjylland, [name], 5 Ear, nose and throat department, Sygehus Lillebælt, [name], 6 Ear, nose and throat department, Sydvestjysk Sygehus, [name].

**Introduction**

Tonsil surgery, with or without adenoidectomy, performed on both children and adults is one of the most frequent surgical procedures in the ear, nose and throat (ENT) specialty worldwide, and the number of tonsil operations has increased over recent decades^1–5^. In Denmark, approximately 7.000 tonsil operations are performed annually^6^ based on benign indications such as recurrent episodes of acute tonsillitis and upper airway obstruction due to adeno-tonsillar hypertrophy^7^.

Although, commonly performed, tonsil surgery is associated with significant morbidity^3^, such as postoperative pain and more severely post tonsillectomy hemorrhage (PTH)^7–12^. Postoperative pain lasts for approximately two weeks, and may in severe cases result in delayed discharge, a visit at the emergency department or readmission for pain control, hydration, and treatment of possible underlying infection^3^. The incidences of PTH vary between 0.3 and more than 10%^1,11,13,14^ and is a major and potential life-threatening complication of tonsil surgery^3,8^.

Because the evidence base of tonsil surgeries in Denmark is low, it is recommended in the Danish National Clinical Guideline from 2019^15^ , to secure the monitoring of tonsil surgeries via a uniform registration of procedures and diagnoses in Denmark. Further recommendations^15^ are that tonsil surgeries are monitored via a database, that can register the surgical method, the extent of the surgery (tonsillectomy vs. tonsillotomy), and length of postoperative hospital stay which is not properly described in Danish patients^15^. The criteria for offering patients tonsil surgery vary in Denmark, and the diagnostic criteria are not well-defined for especially recurrent acute tonsillitis and chronic tonsillitis^15^. There is also believed to be a variation in the applied surgical techniques especially on which instruments are used for the removal. Such data can be obtained from properly designed clinical databases^16^.

The Danish Tonsil database is a population based clinical database established in 2017 in the Central Denmark Region. It is a copy of the concept underlying The National Tonsil Surgery Register in Sweden (NTSRS), which was founded in 1997 covering more than 80% of all tonsil surgeries in Sweden. Several retrospective studies based on data from the register have been published^8,17^.

From 2021, ENT departments of the Region of Southern Denmark, and the North Denmark Region have entered the Danish tonsil database collaboration. The database contains pre-, per-, and postoperative information about tonsil surgery, including surgical method and instruments.

Although cold steel tonsillectomy is considered the gold standard surgical technique, several hot techniques including bipolar techniques, diathermy, and coblation have been developed for tonsillectomy^2^. Hitherto, these hot instruments have not proven superior to the gold standard in terms of reducing PTH, and it is recommended, that these hot techniques should be used with caution^2,3,5,8,18,19^. In cold steel tonsillectomy the peritonsillar space is dissected with metal instruments, and bleeding is typically controlled by ligation or electrocautery.

Recently, a new impedance-dependent tissue sealer (IDTS) device (BiZact^TM^) has been approved for all benign indications for tonsillectomy^20^. Preliminary results are promising in terms of a PTH rate of 4.5%, a shortened operative time with a median time of 5.1 minutes (range 1.5-26.5 minutes), and a reduced intraoperative blood loss to 1-10 milliliters^20^. With the IDTS the peritonsillar space is dissected and sealed in one step using adjustable energy from a ValleyLab FT10 Energy Platform (Medtronic) measuring the impedance of the tissue grasped with the instrument securing hemostasis before the surgeon cuts the tissue.

Ideally, if a gold standard technique is to be replaced by a new technique, it is recommended that the decision should be based on scientific studies performed as randomized designs.

**Primary objective**

The aim of the study is to evaluate whether tonsillectomy performed with an IDTS is non-inferior compared to tonsillectomy performed with cold steel instruments in terms of PTH and postoperative pain.

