**Outcome Assessment**

Primary endpoints:

- Incidence of PTH defined as hemorrhage requiring hemostasis with bipolar electric coagulation, ligature, compression and/or medical treatment with anti-fibrinolytic within the first 24 hours after surgery (early PTH) until 30 days after surgery (late PTH).
- Intraoperative blood loss assessed by a standardized protocol utilizing the gravimetric method. The nurse suctions up 100 ml of NaCl weighed on the scale for precision (Kern & Sohn, PCB 6000-1). The suction canister is also weighed on the scale, as well as the dry gauze. After the surgery the canister of blood including the NaCl is weighed and the dry weights of the canister and gauze including the NaCl are subtracted, this leaves the total blood loss of the operation. It is assumed that 1 gram blood = 1 ml blood.
- Operative time in minutes from the Boyle-Davis gag is placed until it is removed. The operating nurse is responsible for measurements of time.
- Postoperative pain is assessed on an 11-point numeric rating scale ranging from 0 “no pain” to 10 “worst possible pain”. For children, the Wong-Baker Faces rating scale will be used.

Secondary endpoints:

- Patient reported: Unscheduled contacts to the health care system, patient satisfaction, health related quality of life, and patient reported quality of smell and taste via a validated TASTE questionnaire, followed by further investigation should the patient report altered taste at six months.

Variables:

- Patient reported outcome measures (PROMs) of postoperative recovery (return to normal diet, physical activity, and return to work, school, or childcare), compliance to postoperative recommendations.

**Inclusion criteria:** First time tonsillectomy due to; Tonsillar hypertrophy, recurrent tonsillitis (including previous peritonsillar abscess), chronic tonsillitis, systemic complications to tonsillitis, other (mononucleosis), PFAPA (periodic fever, aphthous stomatitis, pharyngitis, cervical adenitis), tonsillar plugs, peritonsillar abscess and signed written consent.

**Exclusion criteria:** Diseases in the hematopoietic system, antithrombotic or anticoagulant drugs in the recovery period, suspicion of or known malignancy, patients, or parents unable to read or speak Danish, patients, or parents unable to use online application for self-evaluation, patients or parents unable to give informed consent, body weight under 16 kilograms.

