**Statistical analysis**

Endpoints will be evaluated as differences between treatment groups. Categorical data are analyzed by chi2 or Fisher’s exact test. Depending on normal distribution, continuous data is analyzed by either un-paired Student’s *t-test* or Mann-Whitney rank sum test. An Intention-to-treat principle will be used including all randomized participants in the analysis. Stratification will be performed, and confounding factors (sex, age, surgical indication, BMI, smoking, comorbidity) analyzed in a multiple logistic regression model. Repeated measurement data will be analyzed in a mixed effect model for repeated measurements (ANOVA) with group and time as systematic factors and patients as random effect. The model takes random variations over time into account. Post-hoc tests will be based on the Kenward-Roger approximation to test all included patients despite missing data. The significance level is set at 0.05.

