**Discussion**

This protocol describes a Danish randomized controlled multicenter trial with the primary aim to evaluate whether IDTS tonsillectomy is non-inferior compared to cold steel tonsillectomy with regards to PTH and pain.

The study has four key strengths. The study is a randomized controlled trial with block randomization securing that patients are consecutively enrolled in the surgical treatment groups, a vital step to avoid selection bias. A further key strength is the multicenter setup considered the ideal way to generate data ready for generalization and enabling the enrollment of the large number of participants required for the protocol. In this study the multicenter setup entails cooperation of three regions including five treatment centers, hereunder as well secondary and tertiary treatment centers. The setup ensures a wide population-based inclusion in the project. Furthermore, the project will be both assessor blinded and blinded for the patients to prevent observer and confirmation bias.

There are also limitations to this study. The most significant limitation of the study is the lack of definition of PTH worldwide. The literature thoroughly describes primary and secondary bleeding occurring before and after 24 hours, respectively, but without a clear definition of severity. In this study we will define severity by interventions needed for PTH to accommodate this.

A potential limitation for the study is also one of the strengths - the multicenter setup inhabits a risk of one center not enrolling to equal measure of other centers, thereby entailing a selection bias. To remedy the selection bias of the center the dataset will potentially have to be excluded, which will weaken the results. The comprehensive logistics of multicenter studies sometimes result in unexpected heterogeneity in clinical practices between centers, which may induce confounders affecting the interpretation of the results.

In our study we have daily patient reported outcomes on pain management, which potentially will alter the patients’ compliance, also called the Hawthorne effect.

To our knowledge, the present study is the largest randomized controlled trial in ENT surgery in the Nordic countries to test the hypothesis whether IDTS tonsillectomy is non-inferior to cold steel tonsillectomy with regards to PTH, surgery time and postoperative pain.

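### The protocol gives three different sets of primary outcomes, sizes and sets a margin for only one (PTH), and states no rule for what counts as trial success

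*Protocol*

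**What the plan says.** The protocol describes what is primary in three ways.

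- **Primary objective:** IDTS is to be shown "non-inferior compared to tonsillectomy performed with cold steel instruments in terms of PTH and postoperative pain". The opening of the Discussion repeats this pair as the primary aim.
- **Outcome Assessment, primary endpoints:** four items of equal standing. They are "Incidence of PTH defined as hemorrhage requiring hemostasis with bipolar electric coagulation, ligature, compression and/or medical treatment with anti-fibrinolytic"; "Intraoperative blood loss assessed by a standardized protocol utilizing the gravimetric method"; "Operative time in minutes from the Boyle-Davis gag is placed until it is removed"; and pain ("Postoperative pain is assessed on an 11-point numeric rating scale", with a faces scale for children).
- **Discussion, closing paragraph:** the hypothesis is that IDTS is "non-inferior to cold steel tonsillectomy with regards to PTH, surgery time and postoperative pain".

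Power Considerations gives one margin (4%) and one sample size (1126, raised to 1250 for dropout). Both are for PTH that leads to reoperation. Statistical analysis lists chi-squared, Fisher, t and Mann-Whitney tests, a logistic model and a repeated-measures model, and ends with "The significance level is set at 0.05". It does not rank the four primary endpoints, divide the level between them, or say whether one or all must succeed.

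**The concern.** A reader of the final report must be able to tell from the protocol which result decides the trial. Here that cannot be done. Blood loss is a primary endpoint that appears in no stated aim. Surgery time has a non-inferiority hypothesis in the Discussion but is absent from the objective. Pain is half of the stated aim as a non-inferiority claim, yet it has no margin, and the listed methods test for differences. A non-significant difference does not establish non-inferiority.

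The practical risk is selective success. The Introduction already describes shorter operating time and lower blood loss with IDTS as promising. Under the protocol as written, a gain on either could be reported as a primary endpoint met even if PTH, which the Introduction calls potentially life-threatening, failed its margin.

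**Working it through.** **1. What the sample size covers.** Inputs from Power Considerations: PTH 7.9% (taken as equal in both arms), margin 4% (read as 4 percentage points), power 80%, significance level 0.05 with sidedness not stated. Allocation is 1:1 (Design).

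n per arm = 2 × p(1−p) × (z₁₋α + z₀.₈)² / margin²

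- One-sided 0.05: 2 × 0.079 × 0.921 × (1.645 + 0.842)² / 0.04² = 562.3, so 563 per arm and 1126 in total. This matches the protocol exactly.
- One-sided 0.025: 714 per arm, 1428 in total. This does not match.
- Dropout: 1126 / 0.9 ≈ 1251, or 1252 in equal arms, against 1250 stated. The gap is negligible.

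The stated N therefore comes from PTH inputs alone. No other primary endpoint enters it.

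**2. The outcome sets side by side.**

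| Outcome | Primary objective | Primary endpoint list | Closing hypothesis | Margin and N |
|---|---|---|---|---|
| PTH | yes | yes | yes | yes |
| Pain | yes | yes | yes | no |
| Operative time | no | yes | yes | no |
| Blood loss | no | yes | no | no |

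**3. If any one primary endpoint may carry the claim.** Suppose each is tested at 0.05 and all null hypotheses are true. With independent tests:

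- two outcomes: 1 − 0.95² = 9.75%
- three outcomes: 1 − 0.95³ = 14.3%
- four outcomes: 1 − 0.95⁴ = 18.5%

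Simulating four two-sided tests with a common correlation (assumed, since the protocol gives none) yields 18.0% at 0.2, 15.6% at 0.5 and 11.4% at 0.8.

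**4. If all must succeed.** The false-positive rate is not inflated, but power falls. Joint power cannot exceed the power of the weakest component, so at best it equals the 80% for PTH. How far below that it lies depends on the power for pain, operative time and blood loss. The protocol gives no margin, effect or standard deviation for any of them.

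**5. How sensitive the continuous endpoints are.** With 563 per arm, a two-sided 0.05 t-test has 80% power for a difference of (1.96 + 0.84) × √(2/563) = 0.17 standard deviations. A small saving in time would be enough for a significant result.

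**6. What each success rule would require for PTH.**

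- PTH as single primary: N is unchanged at 1126/1250.
- Any one of four with an equal split: one-sided 0.05/4 = 0.0125 gives 865 per arm, 1730 evaluable, about 1923 with dropout. At the planned 563 per arm, PTH power would be 59.7%.

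**The case against.** The strongest reply is that only the protocol is at hand. A multiplicity procedure, the pain summary measure and the handling of adult and child scales are often left to the SAP. The body of Table 1, which covers timing and definitions, is also not in the text. This stands: the absence of a pain time point, a summary or an alpha procedure is not a finding here. It does not resolve the conflict between sections, because the objective and the primary endpoints are set in the protocol and disagree there.

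The second reply is that the surgery-time wording occurs only in a closing sentence about the size of the trial, so the real conflict is between the objective and the endpoint list. That is fair on weight. The sentence is nevertheless phrased as the hypothesis under test and should agree with the rest.

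Third, the error figure is conditional. The protocol states one general level, so testing each endpoint at an unreduced 0.05 is a reading, although nothing shown reduces it. The 18.5% also needs an any-one-suffices rule, which the protocol does not state, and independence. Counting only errors that favor IDTS, with PTH and pain at one-sided 0.05 and the other two at 0.025, gives 1 − 0.95² × 0.975² = 14.2%.

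Two stronger readings are tempting but unsupported. A reader might treat every daily pain score as a further independent chance of a false positive. The scores are repeated measurements in the same patients and are analyzed in one model, and nothing says a single day could carry the claim. A reader might also multiply 80% by 80% to obtain a joint power for PTH and pain. The protocol gives no power for pain, and a continuous score in 563 patients per arm could well have more than 80%.

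**Conclusion.** The point holds as an internal contradiction with a missing success rule. The three descriptions of what is primary cannot all be right, and only PTH is designed as a non-inferiority question. Non-inferiority on pain or on surgery time cannot be concluded from this protocol without a margin.

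The size depends on a rule the protocol does not state. If any one of four suffices at 0.05, the false-positive chance is up to 18.5% for independent tests and about 11% to 18% at the assumed correlations. If all must succeed, the stated 80% describes PTH alone, and the loss in joint power cannot be computed. The sample size is not at fault: it reproduces for PTH at one-sided 0.05. The contradiction should be settled before results by arm are seen. Confidence is high on the contradiction and the missing margins, and moderate on multiplicity, which an SAP might address.

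**What to change.** - Name PTH non-inferiority with the 4-point margin as the single primary endpoint.
- Use one PTH definition throughout. Outcome Assessment counts any hemostatic intervention, including compression and anti-fibrinolytic treatment, while Power Considerations counts only PTH leading to reoperation. The 1126/1250 is kept if the 7.9% and the margin apply to the definition chosen.
- Make the Primary objective, the endpoint list and both statements in the Discussion agree.
- Make pain, operative time and blood loss key secondary endpoints, tested at 0.05 in a fixed, stated order and only after PTH non-inferiority is shown. Remove non-inferiority wording wherever no margin exists.

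The cost is wording in the protocol and registry, with no added patients. The real downside is that three outcomes lose primary status and pain leaves the primary aim, which changes the question the trial says it answers.

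Keeping PTH and pain as co-primary is a valid alternative. The sponsor would then have to state that both must succeed, set a pain margin and one summary measure, and restate the power as joint power. No division of the 0.05 would be needed.

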**Method**

*Design*

The project is designed as a Danish randomized controlled multi-center trial of tonsillectomy by conventional cold steel surgical technique versus IDTS. The study is blinded for patients until six months after surgery and the study is assessor blinded.

Randomization is computerized via the tonsil database and utilizes block randomization for each department in a random table of 2000 with equal numbers of group assignments. The randomization is only apparent to the surgeon on the day of the surgery and the day before.

*Course*

All elective and acute patients referred to tonsillectomy, with or without adenoidectomy, on benign indications will be assessed for eligibility at the participating ENT departments. Given a signed declaration of consent patients will be enrolled and randomized in the study to either the standard cold steel tonsillectomy or to IDTS tonsillectomy.

After surgery all patients will be brought to the recovery room for 1-4 hours or hospitalized for a day. Before hospital discharge a surgeon will check for postoperative hemorrhaging and the patient and caregivers will receive oral and written recommendations for the postoperative period. Patients or caregivers are requested to follow the recommendations, and they are instructed to contact the ENT department or to call an ambulance, if postoperative hemorrhage occurs.

There will be no planned postoperative visits at the hospital. During the first six postoperative months included patients/caregivers are asked to complete electronic questionnaires online on their mobile device: daily, for the first two postoperative weeks, and again one month and six months postoperatively.

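### The unqualified assessor-blinding claim is wrong for operative time and blood loss, and the protocol does not secure it for post-tonsillectomy hemorrhage

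*Protocol*

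**What the plan says.** Under Method, Design, the protocol states that patients are kept blind for six months and that "the study is assessor blinded". The same section limits who sees the allocation: "The randomization is only apparent to the surgeon on the day of the surgery and the day before." The Discussion lists blinding among the trial's strengths, saying that "the project will be both assessor blinded and blinded for the patients to prevent observer and confirmation bias". No section names the blinded assessors or the endpoints they assess.

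Outcome Assessment lists four primary endpoints: PTH, intraoperative blood loss, operative time and postoperative pain. It describes their measurement as follows.

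- **Operative time:** "The operating nurse is responsible for measurements of time." The clock runs from placement to removal of the gag.
- **Blood loss:** a weighing procedure carried out around the operation, in which "The nurse suctions up 100 ml of NaCl weighed on the scale for precision".
- **PTH:** bleeding that needs one of several interventions, counted to 30 days. Compression or an anti-fibrinolytic is enough. According to the Figure 2 legend, a doctor enters the details in the tonsil database. The Introduction says this database records surgical method and instruments.
- **Pain:** reported by the patient, or with the caregiver for children.

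**The concern.** Calling a trial assessor blinded tells the reader that whoever generated the outcome data did not know the treatment. Here the arms differ in the instrument held in the surgeon's hand: metal dissection instruments, or a sealer connected to an energy platform. Staff measuring outcomes in that theatre cannot plausibly be masked, and no masking step is described for them.

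PTH matters more, because it is part of the primary objective and it sizes the trial. An endpoint defined by treatment given is partly a record of clinical decisions. If the deciding or recording doctor knows the instrument, the threshold for treating or recording a minor bleed could differ between arms. In a non-inferiority comparison with a 4-point limit, a small difference of this kind could move the result in either direction.

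**Working it through.** **Step 1. Set the claim against each listed primary endpoint.**

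| Endpoint | Who produces the value | Masking in the text |
|---|---|---|
| Operative time | Operating nurse, in theatre | None described; knowledge of the instrument inferred |
| Blood loss | Nurse, by weighing | None described; knowledge of the instrument inferred |
| PTH | Doctor decides to treat; doctor enters it | None described for either step |
| Pain | Patient or caregiver | Patients blinded to six months |

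For operative time and blood loss, 2 of 4, the claim conflicts with the measurement procedure. What the nurse knows is an inference from the setting, as the protocol does not state it.

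**Step 2. Compare the visibility window with the PTH period.** Allocation is apparent to the surgeon on the day before surgery and the day of surgery. Early PTH is the first 24 hours, so it overlaps the window. Late PTH runs from 24 hours to day 30 and lies outside it. However, the text does not say whether the instrument field stays viewable in the database after the window closes, or whether the doctor who treats or records a late bleed may have been the operating surgeon. Late PTH may be masked in practice, but the protocol does not secure it.

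**Step 3. Reproduce the sample size, so that any illustration uses the trial's own terms.** Power Considerations gives 7.9%, a 4-point limit, 80% power and a significance level of 0.05. With one-sided 0.05:

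n per arm = (1.645 + 0.842)² × 2 × 0.079 × 0.921 / 0.04² = 562.3, so 563 per arm and 1126 in total.

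This matches the stated 1126. One-sided 0.025 gives 714 per arm (1428) and does not match. Allowing for 10% dropout, 1126 / 0.9 = 1251, against 1250 stated. Nothing in this point changes the sample size.

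**Step 4. Illustration only: sensitivity to an assumed recording shift.** Let the recorded PTH rate in the tissue-sealer arm differ from the true rate by 1 or 0.5 points. Both sizes are assumptions, and the direction is unknown. SE is taken at the recorded rates, for 563 to 625 per arm.

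- *True excess of 4 points (7.9% v 11.9%), sealer rate recorded too low by s.* The chance of falsely declaring non-inferiority is Φ(s/SE − 1.645). For s = 0.01 and n = 563, SE = √[(0.079 × 0.921 + 0.109 × 0.891)/563] = 0.01737, giving Φ(0.576 − 1.645) = 14.2%. For n = 625 it is 15.0%. For s = 0.005 it is 8.7% to 8.9%. The nominal value is 5%.
- *Same true excess, sealer rate recorded too high by 1 point.* The chance falls to 1.3% to 1.4%.
- *True equality at 7.9%, sealer rate recorded too high by 1 point.* Power is Φ((0.04 − 0.01)/SE − 1.645). With SE = 0.01653 at n = 563, this is 57%, compared with 80% without the shift. At n = 625 it is 61%, compared with 84%.

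The 7.9% is a rate of PTH causing reoperation. The rate of minor bleeds, where discretion is greatest, is not given. The figures therefore show how sensitive the comparison would be and do not estimate a bias in this trial.

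**The case against.** The strongest reply is that the practical exposure is small. Weighing under a standard procedure and timing between two defined events leave little room for an observer's expectations. Neither endpoint appears in the Primary objective section or drives the sample size, so the 4-point limit does not apply to them. All of this stands. It limits the consequence for these two endpoints but does not make the label true for them.

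For PTH, the visibility restriction can fairly be read as a masking measure that covers most of the 30 days. Blinded patients also decide whether to seek care for a bleed after discharge, so that step is masked. Both points stand. What remains is overlap with the window for early PTH and unsecured masking of the doctor's decision and entry for late PTH.

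Two stronger readings are tempting, and the documents support neither.

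- A reader might infer that the pre-discharge examination unblinds PTH, because "Before hospital discharge a surgeon will check for postoperative hemorrhaging" and allocation is visible that day. The text says *a* surgeon, who need not be the operating one. It also says "After surgery all patients will be brought to the recovery room for 1-4 hours or hospitalized for a day", so for patients kept overnight the check may fall after the window. Nor is the check described as the way PTH is ascertained.
- A reader might infer that pain is the only outcome with described blinding. Satisfaction, quality of life, smell and taste, and unscheduled contacts are also reported by patients blinded to six months.

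**Conclusion.** The point holds in a limited form. The unqualified claim in Design and in the Discussion is wrong for two of the four listed primary endpoints. This rests on one inference, that theatre nurses see the instrument in use. For PTH the claim is unsecured rather than shown to be false: early events can fall within the visibility window, and nothing in the text guarantees that the doctor who decides on or records a late event is masked. Patient-reported outcomes are adequately covered by patient blinding.

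A reader might take the 14% to 15% in the working as this trial's false-positive risk. It is not. The shift is assumed, it could equally run the other way and cost power, and it is applied to a reoperation rate that is less open to discretion than minor bleeds. The conclusion depends on no figure. The correction is still worth making: as written, readers will credit the trial with a protection it does not describe for operative time, blood loss and, in part, PTH.

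**What to change.** 1. In Design, describe the trial as patient-blinded to six months, with operative time and blood loss recorded unblinded in theatre.
2. In the Discussion, limit the observer-bias claim to endpoints with masked assessors: patient-reported outcomes, and PTH only where masking is secured.
3. In the tonsil database, keep the allocation and instrument fields hidden from the doctor completing the PTH form, and say so in the protocol. If this is already the case, one sentence is enough. This masks the entry but not the decision to treat, hence the next item.
4. Report PTH needing reoperation as a sensitivity analysis. It is the component behind the 7.9% and is less discretionary than compression or drug treatment.

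The cost is a less favourable blinding statement, one database display setting and one extra analysis. The sample size does not change.

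### The surgeon can see the allocation from the day before surgery, and nothing in the protocol fixes the operator or the date before then

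*Protocol*

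**What the plan says.** Under Method, Design, the Protocol describes computerised allocation through the tonsil database. It "utilizes block randomization for each department in a random table of 2000 with equal numbers of group assignments". On disclosure it says: "The randomization is only apparent to the surgeon on the day of the surgery and the day before".

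On sequence, Method, Course says: "Given a signed declaration of consent patients will be enrolled and randomized in the study". The legend to Figure 2 gives the same order: consent, then data entry by the surgeon, then assignment by the computer.

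On blinding, the Design section says: "The study is blinded for patients until six months after surgery and the study is assessor blinded". It makes no claim that surgeons are blinded. The Figure 2 legend adds: "The per-operative procedure is equal for both groups as well as postoperative recommendations".

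The Discussion credits the allocation method with protection against bias: "block randomization securing that patients are consecutively enrolled in the surgical treatment groups, a vital step to avoid selection bias".

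The Statistical analysis section specifies intention-to-treat on all randomised participants and a multiple logistic regression with sex, age, surgical indication, BMI, smoking and comorbidity. It also mentions stratification without naming the factors.

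The Protocol does not say that the operator or the surgery date is settled before disclosure, that a later change of either must be recorded, or why the surgeon needs the arm a day ahead.

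**The concern.** A surgeon needs to know the arm once the operation is to begin. Access from the previous day opens a window in which the operator can be swapped or the case postponed in the light of the arm. No misconduct is needed. The Introduction presents the tissue sealer (IDTS) as a recent device and cold steel as the established standard, so familiarity may well differ between colleagues. Giving device cases to those who know the device, or cold steel cases to trainees, would be ordinary list planning.

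Three of the four primary endpoints (PTH, blood loss and operative time) plausibly depend on who operates. If operators are sorted by arm, the trial compares technique plus operator. Randomising within department balances departments, not the operators inside them. Blocking, which the Discussion credits, balances numbers and has no effect on decisions taken after the arm is known. In a non-inferiority trial the distortion could hide a real excess of PTH or make an acceptable technique fail.

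**Working it through.** **1. What could be decided with the arm known**

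- Enrolment: no. Consent and randomisation come before disclosure.
- Operator: yes. No rule fixes it first, and neither intention-to-treat nor the listed covariates balance it.
- Postponement: yes, but under intention-to-treat the patient stays in the assigned arm.
- Withdrawal: yes, but it biases the result only if the outcome is then lost, and lost selectively.

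Operator choice is therefore the main route.

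**2. The plan's own figure**

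Inputs from Power Considerations: PTH rate 7.9%, margin 4 points, significance level 0.05, power 80%. With equal true rates and a one-sided 5% test:

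n per arm = (1.645 + 0.842)² × 2 × 0.079 × 0.921 / 0.04² = 6.183 × 0.1455 / 0.0016 = 562.3, so 563 per arm and 1126 in total.

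This matches the stated 1126. (A one-sided 2.5% test would need 714 per arm, 1428 in total, so 5% one-sided is what was used.)

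**3. Size of a possible operator bias**

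The Protocol gives no operator effect and no rate of operator changes. Both inputs are assumptions:

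- d: difference in PTH rate between two groups of operators, 2 to 4 points;
- s: difference between arms in the share of cases done by one group, 10 to 30 percentage points.

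Bias = s × d.

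| s | d = 2 points | d = 4 points |
|---|---|---|
| 10 percentage points | 0.2 | 0.4 |
| 20 (60% v 40%) | 0.4 | 0.8 |
| 30 (65% v 35%) | 0.6 | 1.2 |

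The range is 0.2 to 1.2 points, that is 0.2/4 = 5% to 1.2/4 = 30% of the margin. With s = 0 there is no bias.

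**4. Effect on the non-inferiority test (563 per arm, one-sided 5%)**

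*Bias in favour of IDTS, which is truly 4 points worse (11.9% v 7.9%).*
SE = √[(0.079 × 0.921 + 0.119 × 0.881)/563] = 1.78 points.
Chance of a false non-inferiority claim = Φ(bias/1.78 − 1.645):

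- bias 0: 0.05
- bias 0.2: 0.063
- bias 0.8: 0.116
- bias 1.2: 0.166

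*Bias against IDTS, true rates equal at 7.9%.*
SE = √(2 × 0.079 × 0.921/563) = 1.61 points.
Power ≈ Φ((4 − bias)/1.61 − 1.645), ignoring the small change in SE that the bias causes:

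- bias 0: 0.80
- bias 0.2: 0.76
- bias 0.8: 0.64
- bias 1.2: 0.54

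**The case against.** The disclosure sentence is a restriction. It names one role and a two-day window, and the arm is hidden before that. Late disclosure is thus already in the plan, and the dispute is over about one day. The arm is shown to the surgeon, not to those who build the lists, and the natural reading is that this surgeon is already assigned to the case. No passage describes a swap. IDTS also runs on a specific energy platform, which is a plausible reason for short notice. The illustration has no source: a 4-point operator effect equals the whole margin and is about half the 7.9% base rate.

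Much of this stands. It would be wrong to say the plan abandons late disclosure, and the size of any bias cannot be derived from the document. What remains is that an assigned surgeon who knows the arm can still hand the case on or move it, and the Protocol neither prevents this nor has it recorded.

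A reader might go further in three ways that the document does not support.

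- *Selection at enrolment.* The surgeon enters the patient data ("Patient information is entered into the tonsil database by the surgeon"), but that step comes before allocation, and so do consent and randomisation.
- *A broken patient blind.* An aware surgeon may meet the awake patient, but the Protocol does not say who prepares the patient. Access on the morning of surgery alone would allow the same contact.
- *An analysis that cannot correct the problem.* The listed factors do not include the operator, but the stratification factors are unnamed, and the contents of Table 2 (data entered by physicians) and the SAP are not available. Operator may be recorded and modelled.

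**Conclusion.** The point holds as a vulnerability created by a stated rule. The arm is visible to the surgeon from the day before surgery, nothing fixes the operator or the date first, and the analysis as described does not balance operators. The risk is bias after randomisation, through operator choice above all. Postponement and withdrawal are lesser routes.

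Whether any bias will arise, how large it would be and which way it would run are unknown. The range of 0.2 to 1.2 points rests entirely on the assumed operator effects and shares, and shows only that the possible bias runs from negligible to a material part of the 4-point margin. The change is worth making because it is cheap and because operators sorted by arm are hard to disentangle afterwards. It is an improvement to the conduct of the trial, not a reason to doubt the randomisation itself.

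**What to change.** Amend Method, Design as follows.

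1. Before the database releases the allocation, the named operating surgeon and confirmation that surgery goes ahead must be entered and time-stamped.
2. The allocation is released on the day of surgery, as close to the start as is practical. Release once the patient is anaesthetised, with both instrument sets at hand, is one way to do this but not the only one.
3. Any later change of operator, or postponement, is logged with its reason and tabulated by arm.
4. If equipment logistics need notice the day before, it goes only to theatre staff who take no part in scheduling, and the Protocol says so.

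Step 1 deals with most of the risk even if the timing of release has to stay as it is.

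The cost is a short amendment and, presumably, a modest change to the database, whose technical effort the Protocol does not allow one to judge. The downside is less notice for the surgeon and some extra theatre preparation.
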